### Primary Outcome

The primary outcome measure is the recurrence of incontinence after 1 month after initiation of withdrawal of the physician-prescribed medication, assessed by a self-reported 14-day calendar of incontinence episodes. In addition, recurrence of incontinence after 3, 6, and 12 months after initiation of withdrawal will be measured.

### Secondary Outcome

Secondary outcome measures are as follows. Development of symptoms occurring after abrupt withdrawal of the prescribed medication (solifenacin or mirabegron), assessed by self-reported questionnaires on listed symptoms, as a change from baseline up to 30 days after initiation of withdrawal. Development of symptoms occurring after gradual withdrawal of the prescribed medication (solifenacin or mirabegron), assessed by self-reported questionnaires on listed symptoms, as the change from baseline up to 44 days after initiation of withdrawal. Refer to the Multimedia Appendix 1 for the listed symptoms. The questionnaires are constructed by the authors and do not validate or apply CHERRIES (Checklist for Reporting Results of Internet E-Surveys) items.

### Procedures During the Trial

The participant timeline is illustrated in Table 1.

**Table 1 table1:** Schedule of assessment.

Visit	Visit 1 (baseline)	Visit 2	Visit 3	Visit 4	Visit 5 (end of study)
Day	0	30	91	182	365
Visit schedule window	—^a^	±5 days	±5 days	±5 days	±5 days
Type of consultation	Virtual	Phone call	Phone call	Phone call	Phone call
Informed consent	✓	—	—	—	—
Inclusion and exclusion criteria	✓	—	—	—	—
Background information incl. demographics	✓	—	—	—	—
Randomization	✓	—	—	—	—
14-day calendar with incontinence episodes	—	✓	✓	✓	✓

^a^Not applicable.

### Recruitment

The participants will be included in outpatient incontinence clinics at the Department of Pediatrics at Aarhus University Hospital, Aalborg University Hospital, Regional Hospital Kolding, Regional Hospital Esbjerg, and Gødstrup Hospital.

Doctors and nurses specializing in urinary incontinence in the involved departments will be asked to screen patients. Possible eligible participants will be carefully informed orally and in writing about the objectives of the study, possible risks, and the study procedures, and answer questions regarding the study. Doctors and nurses employed at the involved outpatient clinics will call or send a direct note through the electronic patient journal to the coordinating investigator, site investigator, or his or her representative (a nurse with a specialty in childhood incontinence, affiliated with the involved pediatric departments and trained in the protocol).

Possible eligible participants and their parents or legal guardians will be contacted directly by the coordinating investigator, the site investigator, or his or her representative. The procedure for obtaining informed consent is elaborated in the Informed Consent subsection*.*

The site investigator or his or her representative must ensure eligibility. If a possible participant and their parents or legal guardians are willing to participate after the relevant time for consideration, they are invited to visit 1 in the outpatient clinic or by phone or via virtual contact. Here, informed oral and written consent from the parents or legal guardians will be obtained and signed and dated by the parents or legal guardians and an investigator.

### Visit 1

Participants will enter the study after providing informed consent by parents or parental custody holders. Background information (including age, gender, height, weight, urinary incontinence history, any other medical diagnosis, including psychiatric diagnosis, any comedication, or any withdrawal of comedication) will be obtained.

The participant will be allocated to each of the 3 pharmaceutical groups, according to the physician-prescribed medical treatment that the child is receiving. Within each pharmaceutical group, the participant will be randomized 1:1 to the intervention being compared: abrupt withdrawal or gradual withdrawal. The date of initiation of withdrawal of pharmacotherapy will be decided.

### Visits 2, 3, 4, and 5

Follow-up phone consultations with the coordinating investigator or the site investigator are planned 1, 3, 6, and 12 months following initiation of withdrawal. Data collected at the follow-up visits are the status of continence. The participant will fill out a 14-day calendar of incontinent episodes before each visit. Recurrence of incontinence (defined as >2 episodes of incontinence assessed by a self-reported 14-day calendar of incontinence episodes) or no recurrence of incontinence will be registered.

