### Strengths and Limitations

The strength of our study is the randomized multicenter design, encompassing 5 pediatric departments across Denmark. This ensures broad applicability and relevance in daily clinical practice. The study is embedded into and reflects daily clinical practice. The pragmatic design ensures the timely inclusion of patients and excludes participants with relapses of urinary incontinence.

The main limitation is the lack of blinding, which could introduce bias by influencing outcome assessment or potentially introducing placebo effects. Without blinding, investigators and participants are aware of withdrawal allocation, which can lead to biased behavior while answering the questionnaires and data interpretation. Another limitation is no background knowledge about socioeconomic factors.

By conducting the study in real-life settings with medication that is familiar to patients and parents, the findings are more likely to apply to clinical practice, as they reflect the challenges and circumstances encountered in routine medical care. Furthermore, patients are more likely to adhere to treatment protocols involving medications they are familiar with or have easy access to through standard prescriptions, increasing the feasibility of recruitment and retention in the study.

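### The withdrawal start date is set after open allocation, and Table 1 and the text count follow-up from different days

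*Protocol article*

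**What the plan says.** The Visit 1 section gives the steps in this order. The child is placed in a medication group, then "the participant will be randomized 1:1 to the intervention being compared: abrupt withdrawal or gradual withdrawal", and then "The date of initiation of withdrawal of pharmacotherapy will be decided". Strengths and Limitations confirms that "investigators and participants are aware of withdrawal allocation".

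Two time origins are in use:

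- **Table 1** (Procedures During the Trial) places Visit 1, with consent and randomisation, at Day 0, and Visits 2 to 5 at Days 30, 91, 182 and 365, each ±5 days. It has no row for the start of withdrawal.
- **The text** counts from the start of withdrawal. Primary Outcome defines the endpoint as "recurrence of incontinence after 1 month after initiation of withdrawal of the physician-prescribed medication", and the abstract agrees. The section on Visits 2 to 5 says the calls "are planned 1, 3, 6, and 12 months following initiation of withdrawal". Secondary Outcome also counts its 30 and 44 days from initiation.

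On the calendar, the same follow-up section says: "The participant will fill out a 14-day calendar of incontinent episodes before each visit".

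Under Intervention, the abrupt arm stops on the initiation date. The gradual arm takes its dose on alternate days and has stopped completely 14 days after the process begins.

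**The concern.** There are two separate problems.

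First, the start date is a choice made after randomisation, apparently by people who know the arm. If families or staff treat the two strategies differently when choosing it, the interval to the start, the season or school period in which the calendar falls, and the proportion who never start can all differ by arm. Randomisation does not protect against differences that arise after it, and the outcome is self-reported without blinding. This holds even if every visit is counted from initiation.

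Second, the article gives two clocks for the primary assessment. A site that schedules from Table 1 would assess a child with a delayed start too early relative to withdrawal. The arms are not equally exposed to this, because the gradual arm has a further 14 days of alternate-day dosing. An equal delay in both arms would therefore still tilt the comparison, and in the direction of the trial's hypothesis.

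**Working it through.** The plan states no figure for the interval from Visit 1 to the start of withdrawal, so there is none to reproduce. The check is a day count.

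**Inputs**

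- Visit 2 on day V after Visit 1, with V = 30 and a window of 25 to 35 (Table 1).
- Calendar: the 14 days before the visit, days V−14 to V−1 (Visits 2, 3, 4, and 5). For V = 30 these are days 16 to 29.
- Abrupt arm off drug from day L; gradual arm completely off from day L+14 (Intervention).
- L = days from Visit 1 to the start of withdrawal. This is **not in the documents**; the values below are assumed.

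**Clock 1: the text (initiation = Day 0).** A delay moves the visit and the calendar together, so L drops out. For a visit on day 30 or 35 after initiation, both arms have 0 drug or taper days in the calendar. On day 25 the gradual arm has 3 taper days (14 − 11). These come from the visit window and not from any delay, so they are a separate matter.

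**Clock 2: Table 1 (Visit 1 = Day 0).** Overlap with the calendar, bounded between 0 and 14 days:

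- Abrupt: L − (V−14), which is L − 16 at V = 30.
- Gradual: (L+14) − (V−14), which is L − 2 at V = 30.

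| Assumed delay L (days) | Abrupt: calendar days on drug | Gradual: calendar days on drug or in taper |
|---|---|---|
| 0 | 0 | 0 |
| 3 | 0 | 1 |
| 7 | 0 | 5 |
| 14 | 0 | 12 |
| 21 | 5 | 14 |
| 28 | 12 | 14 |

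The gradual arm is affected once L exceeds 2 days, the abrupt arm only once L exceeds 16. Up to L = 14 the gradual-arm days are all taper days, of which about half are dosing days. The visit window changes the counts. With L = 7, the gradual overlap is 10 days at V = 25 and 0 at V = 35. With L = 14, it is 14 and 7 days. The abrupt arm has 0 in these cases, except 3 days at V = 25 with L = 14.

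**What this could do to recurrence (illustration under Clock 2 only).** Assume no true difference between strategies and Poisson episodes. Set the off-drug mean at 2.285 per 14 days, which makes the chance of more than 2 episodes 40%, the abrupt-arm rate in Sample Size Calculation. Assume 1 episode per 30 days on any drug or taper day, close to the upper limit in the continence criterion. With k overlap days the calendar mean is 2.285 × (14−k)/14 + k/30.

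- k = 0: mean 2.285, recurrence 40%.
- k = 5 (gradual, L = 7): 1.469 + 0.167 = 1.636, recurrence 23%, against 40% in the abrupt arm.
- k = 12 (gradual, L = 14): 0.326 + 0.400 = 0.726, recurrence 4%, against 40%.

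This treats every taper day as fully protected. If taper days gave no protection, both arms would stay at 40%. The range at these delays is therefore from no distortion up to the figures shown.

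**The case against.** The strongest reply is that the endpoint definition already fixes the clock. The abstract, Primary Outcome, Secondary Outcome and the follow-up section all count from initiation, and a definition repeated that often should outrank a table header. A reader might infer from the day counts that the primary calendar will pick up days on drug. The documents do not support that: under the initiation-based text no shift arises at any delay, and the table in the working applies only to sites that schedule from Table 1. This stands, and it makes the calendar effect conditional.

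Three further replies have some force:

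- The delays are assumed. No interval of 7 or 14 days appears anywhere, and if withdrawal always starts at Visit 1 the two clocks coincide. This stands.
- A reader might count as a defect that the article states no maximum delay. A condensed article commonly leaves such detail to the full protocol, which is not shown, so it is not a finding here.
- The sequence is read from the order of sentences, and the article does not say when allocation is disclosed. That is a fair caution. Still, it is the natural reading, and the acknowledged lack of blinding does not answer it: the stated limitation concerns answering questionnaires and interpreting data, not choosing the start date.

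The contradiction itself remains. The article presents Table 1 as the participant timeline, five departments recruit, and a start date that has to be decided need not be the day of Visit 1.

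**Conclusion.** The point holds in two parts of different weight.

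As described, the start date is set after open allocation, so the interval to withdrawal, and failure to start, can depend on the arm. This does not depend on which clock is used. Its size cannot be calculated, because the documents give no delays.

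Table 1 and the initiation-based text give different time origins and must be reconciled. The consequence is nil if sites follow the text, and nil for a Day 30 visit if the delay is 0 to 2 days. If sites follow Table 1, assumed delays of 7 or 14 days put about 5 or 12 of the 14 calendar days inside the gradual arm's taper period and none on drug in the abrupt arm, which favours gradual withdrawal. It would be wrong to conclude that the primary result is biased as planned: the article does not say that sites schedule from Table 1, and the affected days are alternate-day taper days rather than days of full treatment. The change is worth making because it is cheap and removes an avoidable arm-dependent choice from an unblinded, self-reported comparison.

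**What to change.** 1. Reconcile Table 1 with Primary Outcome and the follow-up section by making initiation of withdrawal the single Day 0 for all visits and calendars, and show Visit 1 as a separate column before it.
2. For children still to be enrolled, agree the start date and record it in the electronic case report form before the allocation is revealed. Whether to limit the interval, and to what, is for the sponsor.
3. Report the interval from randomisation to initiation, and the number who never start, by arm.

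The cost is a corrected table, a reordered step in the case report form and one descriptive summary. The drawback is a small change of sequence in an authorised trial that is already recruiting. By February 2025, 25 of 216 children had been included, so at that count 191 (216 − 25) could still be enrolled under the new order. The children enrolled under the old order should be identifiable in the report of intervals.

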### Intervention

Eligible children will be randomized 1:1 to either abrupt or gradual withdrawal of the physician-prescribed medication (solifenacin or mirabegron), the children have been treated with before entering the study. Abrupt withdrawal indicates stopping the prescribed medication on the date of withdrawal initiation. Gradual withdrawal involves taking the prescribed applied dosage of the medication every other day over 14 days, with the complete cessation of the medication occurring 14 days after the gradual withdrawal process begins.

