### Withdrawal of Participants and Criteria of Discontinuation of Study

A study participant should be withdrawn from the study if at any time one of the following criteria applies:

Recurrence of incontinence during the course of the study (defined as >2 episodes of incontinence assessed by a 14-day calendar of incontinence episodes).It is the wish of the participant (or their parents or parental custody holder[s]) for any reason (withdrawal of informed consent).The discretion of the investigator is for safety reasons.Severe compliance with study procedure as described in the protocol, as judged by the investigator.The investigator judges it as necessary due to medical reasons.Participants with a condition or a situation that, in the investigator’s opinion, may put the participant at significant risk or may interfere significantly with the participant’s participation in the study.Participants with any other condition or situation that, in the investigator’s opinion, may be valid for discontinuation from the study.

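### Recurrence is read only from a 14-day calendar before each visit, which leaves more off-drug time unobserved in the abrupt arm and does not settle how an early relapse or a relapse withdrawal is counted

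*Protocol article*

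**What the plan says.** The Primary Outcome section reads: "The primary outcome measure is the recurrence of incontinence after 1 month after initiation of withdrawal of the physician-prescribed medication". It is assessed by a self-reported 14-day calendar, and the same measure is repeated at 3, 6 and 12 months.

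The section on Visits 2, 3, 4, and 5 fixes when the calendar is kept ("The participant will fill out a 14-day calendar of incontinent episodes before each visit") and what counts as recurrence ("defined as >2 episodes of incontinence assessed by a self-reported 14-day calendar of incontinence episodes"). On the content of the calls it says: "Data collected at the follow-up visits are the status of continence". Table 1 lists the calendar only at Visits 2 to 5, on days 30, 91, 182 and 365. The row "Visit schedule window" allows 5 days either side.

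The section on withdrawal of participants opens: "A study participant should be withdrawn from the study if at any time one of the following criteria applies". Recurrence is the first criterion listed, and it is again defined by the 14-day calendar.

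Under Intervention the arms lose drug cover at different times: "Abrupt withdrawal indicates stopping the prescribed medication on the date of withdrawal initiation", whereas the gradual arm has "complete cessation of the medication occurring 14 days after the gradual withdrawal process begins".

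Under Statistical Analysis, the 1-month model is followed by models at 3, 6 and 12 months in a shrinking set of children still in the study. Children with recurrence are described only with descriptive statistics.

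**The concern.** Two rules do not fit together. Recurrence exists only on a calendar tied to a visit, yet a child is to leave the study for recurrence whenever it happens. A relapse on day 8, for example, cannot meet the definition from a calendar that starts around day 16. If the child leaves at that point, no sentence says that this is a primary-outcome event. A site could code the child as a recurrence, as no recurrence or as missing, and could defend each choice from the text.

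The unobserved time also differs by arm. The calendar is placed by days since the start of withdrawal, but the arms come fully off drug 14 days apart. Early off-drug relapses in the abrupt arm therefore fall mostly before the first calendar, and those in the gradual arm mostly inside it. The protocol allows for this shift in its secondary outcome, where symptoms are followed for 30 days in the abrupt arm and 44 days in the gradual arm. It makes no such allowance for the primary outcome.

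The stake is the main comparison. Relapses missed mainly in the abrupt arm would work against the hypothesis that gradual withdrawal is superior. From month 3 onward, restricting the models to children who have not yet relapsed conditions on a post-randomisation outcome, so those comparisons are no longer between the groups as randomised.

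**Working it through.** **Inputs from the protocol.** Visit 2 at day 30 ± 5; 14-day calendar; last drug at day 0 (abrupt) or day 14 (gradual); assumed relapse 40% versus 10%; significance level 0.05; power 80%; 64 per group, 72 after 10% dropout, 216 in total.

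**Assumptions.** The calendar is the 14 days just before the visit, and day 0 is the start of withdrawal. The test is a two-sided chi-square without continuity correction. The shares of relapses missed are not in the protocol.

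**The plan's own sample size.** With a mean rate of 0.25:

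n per arm = [1.960 × √(2 × 0.25 × 0.75) + 0.842 × √(0.4 × 0.6 + 0.1 × 0.9)]² / 0.30² = (1.200 + 0.483)² / 0.09 = 31.5, so 32.

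This gives 64 per drug group with both arms together. Then 64 / 0.9 = 71.1, so 72, and 72 × 3 = 216. The stated figures reproduce. After 10% dropout, the pooled comparison has 216 × 0.9 / 2 = 97 per arm.

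**Off-drug days before the first calendar.** The calendar starts on day (visit − 14). Unobserved off-drug days are (visit − 14) in the abrupt arm and max(0, visit − 28) in the gradual arm.

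| Visit 2 on day | Calendar covers days | Abrupt | Gradual | Difference |
|---|---|---|---|---|
| 25 | 11–24 | 11 | 0 | 11 |
| 30 | 16–29 | 16 | 2 | 14 |
| 35 | 21–34 | 21 | 7 | 14 |

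At the day-25 visit, three calendar days (11 to 13) still fall within the gradual arm's taper.

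**Sensitivity A: missed and recorded as no recurrence, abrupt arm only.** The observed abrupt rate is 0.40 × (1 − m), and the gradual rate stays at 10%. Power is computed from the exact binomial distribution of the chi-square test.

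| Share missed (m) | Observed rates | 97 per arm, pooled | 32 per arm, one drug group |
|---|---|---|---|
| 0 | 40% v 10% | 99.9% | 82.8% |
| 25% | 30% v 10% | 95.0% | 53.2% |
| 50% | 20% v 10% | 50.3% | 20.5% |

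The normal approximation at 32 per arm gives 80.6%, 51.6% and 19.8%.

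**Sensitivity B: same share missed in both arms.** At 25% missed the rates are 30% v 7.5%, with power 98.8% pooled and 66.8% in one drug group. At 50% they are 20% v 5%, with power 91.3% and 48.0%. Most of the pooled loss in A therefore comes from the imbalance between arms.

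**Sensitivity C: relapsers missing, abrupt arm only.** The observed rate is 0.40(1 − m) / (1 − 0.40m). For m = 25% this is 0.30 / 0.90 = 33.3%; for m = 50% it is 0.20 / 0.80 = 25%. By the normal approximation, power is 97.4% and 74.4% from 96 randomised per arm, and 60.8% and 33.2% from 32.

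**Later visits.** If the planning rates applied at month 1, the set still at risk would be 97 × 0.60 = 58 abrupt and 97 × 0.90 = 87 gradual. The later models would compare these selected groups.

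**The case against.** A reader might infer that early relapsers are put back on medication, show a dry calendar and disappear from the abrupt arm. The protocol does not support that as fact. It says nothing about restarting medication. A child who relapses early and stays wet would be caught by the day-30 calendar. A false negative needs the relapse to settle, treatment to resume or the child to leave before the calendar is kept.

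Nor does the protocol say that relapse withdrawals are missing. The withdrawal criterion can be read as making recurrence a terminal event that is registered when the child leaves. On its own definition, a child withdrawn under that criterion has a calendar with more than two episodes. This is a fair reading, but no sentence in the article states it.

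The imbalance is also not absolute, since gradual-arm children can relapse during the taper, before their calendar starts. That they would be missed less often is an inference from timing. Nor should the share of the whole year covered by calendars, 4 × 14 / 365 = 15%, be used to describe the primary outcome. By day 30 the calendar covers 14 of 30 days, or 47%.

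On size, the missed shares are hypothetical, and at 25% missed the pooled power stays well above the planned 80%. The full protocol or analysis plan may settle unscheduled relapses. What stands is that the rules the article does state can miss early relapses unequally by arm, and that they restrict the later comparisons to children who have not relapsed.

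**Conclusion.** The point holds in a limited form. As stated, the endpoint leaves about 16 off-drug days unobserved in the abrupt arm against about 2 in the gradual arm before a day-30 visit, and the difference is 11 to 14 days across the visit window. The withdrawal rule, the outcome definition and the later-visit analysis do not together fix how a relapse outside the calendar is counted. Any resulting bias would plausibly run toward no difference.

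The size is unknown. Under the planning rates, with relapses missed in the abrupt arm only, the effect runs from modest (25% missed: 95% pooled power) to serious (50% missed: 50% pooled power). It is larger within a single drug group (53% and 20%). The restriction of later models to children who remain needs no assumption about missed relapses; it is what the text says. The point should be corrected, but it does not show that the primary result will be wrong.

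**What to change.** Reconcile the sections on withdrawal of participants, primary outcome, Visits 2 to 5 and statistical analysis as follows.

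- Define recurrence by each visit cumulatively: more than two episodes in any 14-day calendar up to that visit, or withdrawal for recurrence before it.
- Count a child withdrawn for recurrence as an event at that visit and all later ones, in the full randomised set, never as missing or excluded.
- At the existing calls, record the date of any relapse and any restart of bladder medication. Use restart as an event in a sensitivity analysis only, because it is discretionary in an open-label trial.

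New wording alone cannot recover a brief early relapse that no calendar captured and that did not lead to withdrawal. The relapse date would show how common these are. Running the first calendar from the start of withdrawal would close the gap, at about 16 more diary days per child.

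The cost of the core change is endpoint wording and two fields at calls that already take place. The downside is some added scope for open-label reporting bias, which the protocol already names as its main limitation. With 25 of 216 children included by February 2025, the change could be made early in recruitment. No rule on restarting treatment is proposed; that stays with the clinician.
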